# Walk with Me: a protocol for a pilot RCT of a peer-led walking programme to increase physical activity in inactive older adults

**DOI:** 10.1186/s40814-018-0308-2

**Published:** 2018-06-21

**Keywords:** Randomised controlled trial, Physical activity, Peers, Older adults, Pilot study

## Abstract

**Background:**

Levels of physical activity decline with age. Some of the most disadvantaged individuals in society, such as those from lower socio-economic position, are also the most inactive. Increasing physical activity levels, particularly among those most inactive, is a public health priority. Peer-led physical activity interventions may offer a model to increase physical activity in the older adult population. This study aims to test the feasibility of a peer-led, multicomponent physical activity intervention in socio-economically disadvantaged community dwelling older adults.

**Methods:**

The Medical Research Council framework for developing and evaluating complex interventions will be used to design and test the feasibility of a randomised controlled trial (RCT) of a multicomponent peer-led physical activity intervention. Data will be collected at baseline, immediately after the intervention (12 weeks) and 6 months after baseline measures. The pilot RCT will provide information on recruitment of peer mentors and participants and attrition rates, intervention fidelity, and data on the variability of the primary outcome (minutes of moderate to vigorous physical activity measured with an accelerometer). The pilot trail will also assess the acceptability of the intervention and identify potential resources needed to undertake a definitive study. Data analyses will be descriptive and include an evaluation of eligibility, recruitment, and retention rates. The findings will be used to estimate the sample size required for a definitive trial. A detailed process evaluation using qualitative and quantitative methods will be conducted with a variety of stakeholders to identify areas of success and necessary improvements.

**Discussion:**

This paper describes the protocol for the ‘Walk with Me’ pilot RCT which will provide the information necessary to inform the design and delivery of a fully powered trial should the Walk with Me intervention prove feasible.

**Trial registration:**

*ISRCTN Number*
 ISRCTN23051918. Date of registration, November 18, 2015.

## Background

Many countries, including the United Kingdom (UK), are facing rapid and sustained increases in the proportion of the population aged 65 years or older [1]. The age-related decline in function, quality of life, and increased risk of morbidity, disability and mortality [2] may be offset or delayed by the adoption of more active lifestyles [3]. A physically active lifestyle in older adults is associated with a reduced risk of developing numerous chronic non-communicable diseases [4, 5] and all-cause mortality [6], and a reduction in the risk of falls [7] and sarcopenia [8]. In addition, regular activity has been linked to improved cognitive function and mental health and wellbeing [9, 10] and higher levels of health-related quality of life [11]. However, despite compelling evidence of the benefits of physical activity as we age, two thirds of the adult population report being inactive, with only 22% of 60–64-year-olds, and as few as 7% aged 75+ years engaging in recommended levels of physical activity in Northern Ireland [12]. Therefore, increasing physical activity levels, particularly among the most inactive, is an important aim of current public health policy in the United Kingdom [13].

Several systematic reviews have summarised the evidence about the effectiveness of physical activity interventions among community-dwelling older adults on self-reported physical activity [14–17]. In general, the interventions encouraged older adult to perform a mode of aerobic activity, of which walking was the predominant form. Most of the interventions included in the reviews were effective at producing short-term changes in physical activity, but levels declined substantially in studies that included longer term follow-up (> 6 months). Individual factors (positive affect and self-efficacy) [18] and social factors (such as social support) [19] are associated with long-term maintenance of changes in physical activity. More recent focus has been on how these factors interact with the potential influence of neighbourhood environments to support physical activity in older adults. A recent study concluded that a supportive physical environment (one which is more ‘walkable’) was associated with higher levels of physical activity, especially in individuals who also had higher self-efficacy and social support [20]. This suggests that an intervention designed on an ecological model, to address multiple levels of influence on physical activity behaviours (including individual, social and environmental factors), is likely to be more effective at delivering sustained changes in activity than interventions targeting individual influences only.

Social cognitive theory (SCT) [21] provides a theoretical framework to understand the relationship between personal, environmental and behavioural factors and has been used effectively to design and implement numerous physical activity interventions. SCT states that personal, environmental and behavioural factors are reciprocally influential in determining behaviour and behaviour change [21]. SCT was used in the design of the Walk with Me intervention. Behaviour Change Techniques (BCTs) identified through a systematic review of peer-led physical activity interventions were mapped onto the core set of psychosocial determinants (i.e. self-efficacy, outcome expectations, goals and impediments and facilitators) of SCT. This approach enabled the research team to design an intervention where the peer mentors’ roles were explicit and could be planned to effectively influence personal, environmental and behavioural factors and their role in physical activity behaviour change. Peer mentors are trained, nonprofessional individuals, who share similar demographic characteristics to the target population (e.g. age, life circumstances and cultural background) and possess experiential knowledge of the target behaviour [22]. In the case of promoting physical activity in the Walk with Me intervention, peer mentors’ roles will be designed to have influence on each of the levels of the socio-ecological model. For example, they may provide individual support and motivation through positive reinforcement and knowledge regarding problem-solving strategies [23].

At present, there are few studies designed to address these multiple influences on the physical activity behaviour of community-dwelling older adults. Therefore, theory-based interventions with multiple components addressing the various levels in the socio-ecological model are required. One approach is to develop multicomponent interventions which capitalise on naturally occurring determinants within target populations and sustainable health promotion mechanisms (i.e. peer groups and their influence on physical activity) to promote long-term physical activity behaviour change. Peer-led interventions offer a model that could help overcome many of the barriers identified above. Peer-led behaviour change interventions are a common and effective means of encouraging behaviour change, including physical activity [24]. Peer mentors will be trained to deliver tailored information about changing physical activity and its benefits. They could provide the necessary social support for behaviour change [25], outside of perceived intimidating settings (e.g. gyms). At an environmental level, the intervention will capitalise on the peer mentor’s knowledge of the local area, by having them engage in activity with the participant in their local neighbourhood, (re)familiarising the participant with local opportunities to engage in physical activity.

### Aims and objectives

The study aims to test the feasibility of a complex peer-led, multicomponent physical activity intervention in socio-economically disadvantaged community-dwelling older adults in a pilot RCT.

The objectives of the study are as follows:To test the recruitment, training and management of a group of peer mentors, working in collaboration with community partnersTo test the feasibility of a peer-led walking programme targeting inactive older adults in a randomised controlled pilot study, in order to inform the design of a main trial should the trial prove feasible

## Methods/design

The Office for Research Ethics Committees Northern Ireland (ORECNI) has given ethical approval for the study (REC reference number 14/NI/1330).

### Study design and setting

Using the Medical Research Council (MRC) framework for complex interventions [26], we designed a multilevel peer-led physical activity intervention for older adults, tailored to meet the needs of the local community. The intervention package has been developed after defining appropriate BCTs for inclusion in the intervention. They were used to inform the intervention design by (i) identifying BCTs used in previous peer-led interventions. To identify BCTs employed in previous peer-led interventions, a rapid review of the literature was conducted and the use of BCTs was extracted; (ii) conducting interviews with members of the target population to explore their preferences for, and the perceived feasibility of particular BCTs identified from the rapid review. Based on the outcome of these stages, we will then (iii) conduct a pilot randomised controlled trial (RCT). The trial will provide information on recruitment and attrition rates, intervention fidelity, data on the variability in objective physical activity measurements and the resources needed to support the development of a definitive trial [27].

#### Phase 1: identification of approaches used in previous peer-led interventions

The first phase in the complex intervention model was to gather relevant evidence and theory to develop a logic model for the implementation of the intervention, which included the proposed causal pathways and relevant outcome measures. A rapid review [28] approach was used to update a previous systematic review of peer-led physical activity interventions in adults aged over 18 years [24]. The review was not restricted to interventions only targeting older adults as there have been very few peer-led interventions in this age group, and this would limit the inclusion of potentially useful components. We adopted the same search strategy as that used in the previous review [24].

The purpose of the rapid review was to extract the BCTs from the intervention descriptions. BCTs were independently identified from the intervention descriptions by two researchers using the recently published BCT Taxonomy (v1) [29]. Additional details such as intervention setting, target participants, dose, duration, mode of delivery (e.g. individual, group, website, written materials) and country were extracted and used to inform intervention development. The BCTs were mapped onto theoretical domains [30] and to the determinants of physical activity in older adults. They were then used to help identify causal pathways linking interventions to behaviour change using the approach taken in a previous review by Michie et al. [31] and to inform the choice of additional measures (possible mediators of change) for the pilot RCT. The socio-ecological model was used to provide a framework for a multilevel intervention design [32] that addresses multiple levels of determinants including individual, social and environmental factors. In addition to individual factors (such as feedback on current behaviour), we plan to address social factors, by providing peer mentors to act as a social support for change, and environmental factors by matching the programme to local environmental opportunities. The Behaviour Change Wheel [33] was used to map promising BCTs (those that are effective and feasible to deliver within the proposed context) on components of behaviour which reflect these multiple levels: motivation (reflective and automatic), opportunities (physical and social environment) and capability (physical and psychological). The main output at this stage was a shortlist of proposed BCTs to be included in the design of a pilot RCT.

#### Phase 2: feasibility and acceptability of proposed BCTs

In the next stage, we explored the perceived feasibility and preferences for particular BCTs through face to face semi-structured interviews with a purposive sample of 15 older adults from our target communities. This sample include both genders, a range of ages (from 60 to 70 years) and individuals living in different locations and with varying levels of physical activity.

As in a previous study in socio-economically deprived adults [34], participants were presented with a range of hypothetical strategies to promote physical activity. These strategies were presented and explained to participants in interviews, in order to explore their opinion and how these strategies could best be incorporated into the intervention package. Participants were asked to indicate the most and least appealing of strategies. For each strategy, they were asked what they like and do not like about it, whether they think it would result in them being more active and sustaining that activity, what they perceive as potential problems or barriers to its uptake, and where appropriate, how and when the strategy would best be delivered.

In addition to exploring the acceptability of specific evidence-based BCTs, the interviews investigated older people’s experiences of walking, identifying barriers and facilitators which will inform the intervention design [35]. These interviews allowed exploration of views on how the specific behaviour of walking may be promoted in their peer group. Attitudes, beliefs and social perspectives on BCTs may influence engagement with the intervention, and these were therefore explored prior to designing the intervention. Taking account of the interview findings enabled us to avoid or overcome potential barriers within the intervention design and to incorporate elements which are perceived to facilitate walking.

The interviews were conducted on a one-to-one basis, semi-structured and contained between 5 and 8 questions. This semi-structured construct allows participants to focus on specific topics but to express themselves freely in their comments. The number of interviews required was proposed as 15, but data saturation was reached after 12 interviews. Analysis was based on SCT [21], and we used standard thematic analysis with constant comparison methods [36], so that issues arising in the early interviews could be explored in more detail in later interviews. The detailed findings of this stage will be reported separately.

#### Phase 3: pilot RCT

The aim of the trial is to test the feasibility of conducting a trial of a peer-led walking programme in promoting sustained increases in objectively measured physical activity in order to enhance health and mental wellbeing, increase social engagement and improve quality of life in community dwelling older adults.

We will conduct a pilot RCT with 60 inactive, community-dwelling older adults aged 60–70 years, residing in socio-economically disadvantaged communities. In their seventh decade, adults from socio-economically disadvantaged areas often transition from good health to poor health, from being fit to being unfit, from independence to dependence and may transition from employment to retirement [37]. This age range (60–70 years) therefore can be seen as a transition period, as older adults from socio-economically disadvantaged areas transition from good health to poor health.

Physical activity interventions delivered at points of life transition such as changes in social (loss of companions), economic (retirement) or health circumstances in older adults may be advantageous. Li et al. [37] acknowledged that this ‘transition’ is not necessarily an abrupt change, but may involve a gradual change over time. Whilst retirement from paid employment may lead to change in employment and income, these transitions may not be applicable to many people in disadvantaged communities. Thus, in addressing the identified research priorities of inequalities in health and physical activity participation in socio-economically disadvantaged communities, we will include all 60–70-year-olds in such communities in our target population rather than focusing on retirement.

For this study, socio-economically disadvantaged communities are defined as those falling within the lowest quartile of super output areas (geographical areas of consistent size used to facilitate the calculation on deprivation indices), based on the Northern Ireland Multiple Deprivation Measure (NIMDM) (https://www.nisra.gov.uk/). For ease of administration, the pilot study will be conducted in the South-Eastern and Northern Health & Social Care Trusts, which covers a large geographical area and a mix of urban and rural settings. In doing so, the intervention would fill an identified gap in preventive service provision for older adults who may need support to increase their physical activity levels in order to maintain physical function and independence in daily living.

### Participant recruitment

We aim to recruit 60 participants. Previous research has identified difficulties in recruiting participants from socio-economically disadvantaged communities [38], and thus, a wide range of active and passive recruitment strategies are required. Active strategies will include identification and referral of potential participants through project partners. Passive recruitment methods will include sending study information, along with a letter from their General Practitioner to suitable patients from primary care practices in target communities, distribution of leaflets and posters through primary care practices, community centres, libraries, health centres, faith-based groups and churches, and the email lists and social media outlets of project partners. Those eventually recruited will be asked how they learned of the study. Individuals who wish to participate will be asked to contact the study team by telephone, in writing or by email. The flow of participants through the trial is described in Fig. 1.

**Fig. 1 Fig1:**
[figure not shown]
CONSORT flow diagram for the Walk with Me trial

#### Inclusion criteria

Participants will be eligible for the pilot trial if they meet the following inclusion criteria:Male or female aged 60–70 yearsLiving in a socio-economically disadvantaged community (defined as the lowest quartile of super output areas according to the NIMDM)Competent to give informed consentNot currently physically active (assessed using the General Practice Physical Activity Questionnaire [39])Community-dwelling (i.e. living in their own home)Planning to stay in the current residence during the next yearAble to communicate in English.No self-reported recent history of myocardial infarction, stroke or physical limitations that would limit ability to participate in a walking programme (assessed using the Physical Activity Readiness Questionnaire [40]).

#### Allocation and randomisation

After contacting the study team, potential participants’ meet with a member of the project team to discuss the study in detail. At this face to face contact, all eligible participants are informed about the details of the project, including what the intervention and the control group will receive and what outcomes are collected. They are advised that participation in the project is voluntary and that they have the right to withdraw consent, at any time, without the need for explanation. They are given a minimum of 48 h to consider participation in the study. After this, those who wish to take part are asked to read, complete and sign a consent form, which will be returned to, and countersigned by a member of the research team. Eligible participants complete baseline outcome measures and are then randomised to an intervention or control group (1:1 ratio) using block randomisation with randomly permuted block sizes. The Northern Ireland Clinical Trials Unit (NICTU) trial statistician will generate the randomisation sequence which will be concealed in sealed envelopes opened by a member of the research team responsible for pairing the mentors and intervention group participants, after completion of baseline measures.

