### Peer mentor training

Peer mentors will be recruited concurrently to participant recruitment through partnerships with local community organisations and charitable organisations. Before being appointed as a peer mentor, these individuals will attend a meeting with a member of the research team at a local community venue where they will be provided with information on the study and their role within it. During this session, potential peer mentors will be asked about their willingness to undergo the required training to deliver the programme and their attitude and commitment to helping others increase their physical activity levels. This session will give the mentor an opportunity to discuss their interests, which in turn helps with the process of pairing the peer mentor with a potential participant. Peer mentors will complete approved background checks prior to being matched with potential participants.

Peer mentors will receive training (2 × 1 h standardised training sessions with the project manager using a peer mentor training and support manual) to develop their skill, knowledge and confidence to promote physical activity among their peers. Training is planned to continue during the programme at regular monthly meetings with mentors, such as providing guidance and support during mentoring sessions. During the training sessions, mentors will receive information on important programme responsibilities. These included a peer mentor’s commitment, main tasks and requirements; information about physical activity guidelines for older adults; education about BCTs and their role in the programme; modelling physical activity behaviours; helping their peer complete programme activities; and reporting on activities or providing feedback to the project team. Mentors will be trained on how to build and sustain an effective mentoring relationship with a peer, as well as skills building in the areas of active listening, communication and providing social and emotional support. A full list of the BCTs to be delivered in the intervention is detailed in Table 1.

**Table 1 Tab1:** BCTs in the Walk with me Intervention

Grouping and BCTs (expanded)	Intervention activities
Goals and planning	
Goal setting (behaviour)	Peer mentors will set or agree on a goal defined in terms of the behaviour to be achieved

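### Allocation is revealed from sealed envelopes by the team member who pairs mentors with intervention participants, not by someone independent of intervention delivery

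*Protocol article*

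**What the plan says.** Under Allocation and randomisation, the article assigns the sequence to the trials unit: "The Northern Ireland Clinical Trials Unit (NICTU) trial statistician will generate the randomisation sequence". Allocation is 1:1 in blocks of randomly varying size; the sizes are not given. The sequence is then "concealed in sealed envelopes opened by a member of the research team responsible for pairing the mentors" with intervention participants, and this happens "after completion of baseline measures". Consent comes earlier, and the form is "countersigned by a member of the research team"; the article does not say whether that person also opens the envelopes.

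Under Peer mentor training, "Peer mentors will be recruited concurrently to participant recruitment". A first meeting with each prospective mentor covers the mentor's interests, which "helps with the process of pairing the peer mentor with a potential participant".

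Under Data analyses, intervention effects are to be given as point estimates with 85% and 95% confidence intervals, by an analyst blind to group. Recruitment, retention and adherence, together with the effect size, are to inform the sample size of a definitive trial.

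**The concern.** Concealment is most secure when the person who reveals an allocation has no reason to care which arm comes up. Here that person must find a mentor for everyone allocated to the intervention. Because mentors and participants arrive over the same period, an envelope may fall due when a mentor is waiting unmatched, or when no suitable mentor is available. Either situation gives a practical reason to prefer one arm for a particular participant, and no bad faith is needed.

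If two or more participants have finished baseline and are waiting, the order in which they are taken to the next envelopes decides their arms. If that order followed mentor fit or apparent motivation, the arms would differ in prognosis from the start. The effect estimate and the adherence seen in the intervention arm would then look better than chance allocation would give, and both feed into the sizing of the definitive trial. A pilot also tests the procedures that the definitive trial would inherit.

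**Working it through.** The plan gives no figure to reproduce on this point, so the first part of the check sets the sections side by side.

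1. **Who reveals the allocation.** Allocation and randomisation names the role: the researcher who pairs mentors with intervention participants. This is a stated choice, not a detail left to a fuller document.
2. **Whether that role is neutral.** Peer mentor training has mentors recruited alongside participants and their interests collected to help pairing. The role therefore works with a mentor supply that varies over time and with information on who would suit whom.
3. **What the existing safeguards cover.** Opening after baseline keeps knowledge of the allocation out of the baseline data and the consent decision. Random block sizes make the next allocation harder to predict. A blinded analyst protects the analysis. None of these fixes the order in which waiting participants are matched to envelopes.
4. **What is not stated.** The article does not say who stores the envelopes, whether they are numbered or logged, whether the trials unit keeps the list, or whether the opener also screens, consents or measures participants.

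**Illustration of size.** Inputs: 60 participants at 1:1, so 60/2 = 30 per arm. Assumption, not in the article: two participants who differ by 1 SD in prognosis for the primary outcome (accelerometer minutes of moderate to vigorous activity) exchange arms, the better one going to the intervention.

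- Intervention mean rises by 1/30 SD and control mean falls by 1/30 SD.
- Shift in the arm difference per exchanged pair = 2/30 = 0.067, or about 0.07 SD.
- For k such pairs the shift is 2k/30 SD; three pairs give 6/30 = 0.20 SD.

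For scale, with complete follow-up of 30 per arm, the standard error of the arm difference in SD units is √(1/30 + 1/30) = √(2/30) = 0.258. One exchanged pair therefore moves the estimate by 0.067/0.258 = 0.26 of a standard error. Unlike sampling error, this shift goes in one direction, and the planned confidence intervals would not reflect it.

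**The case against.** The strongest reply is that this is a recognised method: a sequence from a trials unit, random block sizes, sealed envelopes, and opening only after consent and baseline. Serial numbering, custody, a dated log and an audit against the unit's list are ordinary content of a full protocol, and a condensed article's silence on them is no fault. If those controls exist and are followed, re-ordering is largely prevented. The article also speaks of pairing mentors with people already in the intervention group, and does not say that matches are considered before allocation. All of this stands. It limits the size of the risk but does not change who opens the envelopes.

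Several stronger readings are tempting, and the article does not support them:

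- **That concealment failed, or that this person has a stake in the result.** The article states a role. A reason to prefer an arm is an inference from that role.
- **That this person holds the envelopes and controls when and in what order they are opened.** Only the opening is assigned. Opening before baseline would breach the plan.
- **That the trials unit already holds the sequence and merely declines to release it.** The article says only that its statistician generates the sequence.
- **That the next allocation can be guessed, and that central release would cure this.** Block sizes are not given, so any guess rate rests on assumed sizes. Central release would not lower it, because whoever does the pairing still learns which participants were allocated to the intervention.
- **That recruitment and overall retention would be inflated.** Feasibility is judged on recruitment against the target of 60, attrition at 6 months and qualitative feedback. Exchanging arms does not change who is in the trial, so recruitment is unaffected and overall retention would hardly move.

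**Conclusion.** The point holds as a modest weakness in a safeguard. The stated procedure has allocation revealed by someone who organises delivery of one arm, when independent release would be safer. The exposure is to the between-arm effect estimate and to intervention-arm adherence, which are used to size the definitive trial.

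The figure of 0.07 SD per exchanged pair rests on 30 per arm and an assumed 1 SD prognostic difference. It shows how sensitive a trial of this size is and does not predict that any exchange will occur. The conclusion also assumes that more than one participant may at times be waiting after baseline, which the article neither states nor excludes.

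**What to change.** Amend Allocation and randomisation in one of two ways:

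- **Preferred:** the trials unit that generates the sequence releases each allocation only after the participant has been registered with it and baseline is complete.
- **If envelopes are kept:** an existing team member with no role in pairing opens them in serial order.

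In either case, state that pairing with a mentor starts only after the allocation has been revealed.

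The first option adds a step, a short contact with a unit already engaged, and a small delay for each of about 60 participants. The second needs a different team member to be available at each randomisation, with a similar small delay. Neither changes the design, the sample size or the analysis.
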